## Abstract

**Background:**

Acupuncture is a widely serviced complementary medicine. Although acupuncture is suggested for managing postoperative ileus and pain, supporting evidence is weak. The AcuLap trial is designed to provide high-level evidence regarding whether or not electroacupuncture is effective in promoting gastrointestinal motility and controlling pain after laparoscopic surgery.

**Methods/design:**

This study is a prospective randomized controlled trial with a three-arm, parallel-group structure evaluating the efficacy of electroacupuncture for gastrointestinal motility and postoperative pain after laparoscopic appendectomy. Patients with appendicitis undergoing laparoscopic surgery are included and randomized into three groups: 1) electroacupuncture group, 2) sham acupuncture group, and 3) control group. Patients receive 1) acupuncture with electrostimulation or 2) fake electroacupuncture with sham device twice a day or 3) no acupuncture after laparoscopic appendectomy. The primary outcome is time to first passing flatus after operation. Secondary outcomes include postoperative pain, analgesics, nausea/vomiting, bowel motility, time to tolerable diet, complications, hospital stay, readmission rates, time to recovery, quality of life, medical costs, and protocol failure rate. Patients and hospital staff (physicians and nurses) are blinded to which group the patient is assigned, electroacupuncture or sham acupuncture. Data analysis personnel are blinded to group assignment among all three groups. Estimated sample size to detect a minimum difference of time to first flatus with 80 % power, 5 % significance, and 10 % drop rate is 29 × 3 groups = 87 patients. Analysis will be performed according to the intention-to-treat principle.

**Discussion:**

The AcuLap trial will provide evidence on the merits and/or demerits of electroacupuncture for bowel motility recovery and pain relief after laparoscopic appendectomy.

**Trial registration:**

The trial was registered in Clinical Research Information Service (CRiS), Republic of Korea (KCT0001486) on 14 May 2015.

## Background

With advances in surgery, Enhanced Recovery After Surgery (ERAS) programs enable faster recovery after surgery. The theoretical background of an ERAS program is that minimizing pain and stress in patients undergoing surgery prevents organ dysfunction and complications and consequently enhances faster recovery. The clinical significance of ERAS programs has been proven via many clinical studies. Early enteral feeding with fast bowel motility recovery, and resultant fast recovery and shortened hospital stay are advantages of ERAS programs [1–7].

The key elements of an ERAS program include 1) patient information, 2) preservation of gastrointestinal function, 3) minimization of organ dysfunction, 4) active pain control, and 5) promotion of patient autonomy [8, 9]. Many surgery centers are adopting ERAS programs and trying to enhance recovery of surgical patients by means of preserving gastrointestinal function and adequately controlling postoperative pain.

Meanwhile, we searched the literature to find other factors for recovery of surgical patients, and the literature review revealed that electroacupuncture might have positive effects on postoperative bowel motility recovery and pain control [10, 11]. Accordingly, we assumed that electroacupuncture, which is not included in existing ERAS programs, could accelerate recovery after surgery by means of postoperative pain control and faster bowel motility recovery.

This study aims to evaluate the postoperative effect of electroacupuncture on bowel motility recovery and pain relief in patients undergoing laparoscopic appendectomy.

## Methods/design

### Trial design

The AcuLap trial is a single-center, prospective randomized controlled trial with a three-arm, parallel-group design (Fig. 1). Data analysis will be performed according to the intention-to-treat principle.

**Fig. 1 Fig1:**
[figure not shown]
AcuLap trial flowchart

### Methods: participants, interventions, and outcomes

Patients diagnosed with appendicitis and undergoing laparoscopic appendectomy at Dongguk University Gyeongju Hospital will be recruited.

### Eligibility criteria

#### Patient screening

History taking and physical examinationLaboratory test including CBC (complete blood count), CRP (C-reactive protein), serum chemistry, and urinalysisRadiologic test including abdominal X-ray and CT (computed tomography) scan or ultrasonography.

#### Inclusion criteria

Inclusion criteria include the following:Patients diagnosed with appendicitisPatients over 20 years oldPatients undergoing laparoscopic appendectomy

#### Exclusion criteria

Exclusion criteria include the following:Patients who need simultaneous combined surgery (including ileocecectomy)Patients diagnosed with combined other diseases as well as appendicitis, preoperatively or intraoperatively (such as colonic diverticulitis, inflammatory bowel disease, and pelvic inflammatory disease)Patients who need postoperative fasting according to preoperative evaluation or intraoperative findings (for example, panperitonitis with intraperitoneal abscess)Patients under treatment for acute disease other than appendicitisPatients converted to open surgeryPatients with cardiac pacemakerPatients with allergy to or phobia of acupuncture needle or electrostimulationPatients with history of syncope or seizurePregnant women or lactating womenPatients with history of abdominal surgeryPatients with American Society of Anesthesiologists (ASA) physical status classification IVPatients who do not consent to clinical trialPatients incapable of reading, understanding, and signing a written consent form (for example, people who are mentally retarded, blinded, illiterate, or foreigners)Inmates of a prison or institution/hospital

#### Participating center/physicians

The study will be conducted in the Department of Surgery, Dongguk University Gyeongju Hospital, Korea.

Laparoscopic appendectomy will be performed by three board certified surgeons with minimum experience of 8 years.

Acupuncture will be performed by two board certified oriental medicine doctors with minimum experience of 10 years.

### Interventions

#### Study outline

Patients with appendicitis undergoing laparoscopic surgery are included and randomized into three groups: 1) electroacupuncture group, 2) sham acupuncture group, and 3) no acupuncture group. Patient allocation is performed by block randomization.

After laparoscopic appendectomy, routine postoperative care is equally given to all patients except for interventions (electroacupuncture or sham acupuncture). Clinical outcomes including postoperative pain score and bowel motility recovery are evaluated in each of the three groups during hospitalization. Quality of life and medical cost are evaluated after discharge.

#### Intervention group I: true electroacupuncture

Patients in the electroacupuncture group receive acupuncture with electrostimulation with stainless steel needles and a PG-306 electroacupuncture device after the operation. At least 2 hours after the operation, electroacupuncture is given for 30 minutes, twice a day, with a minimum interval of 4 hours between the morning session and afternoon session, starting on operation day. A maximum of four acupuncture treatments are performed during hospitalization. This acupuncture schedule is set from the literature review [12] and in consideration of the usual hospital stay after laparoscopic appendectomy.

Acupuncture is performed by Korean board certified oriental medicine doctors with 10 years of experience in acupuncture. Acupuncture sites (locations) are the following which are known to control pain and promote gastrointestinal motility: LI4 (Hapgok, Hegu), PC6 (Naegwan, Neiguan), KI6 (Johae, Zhaohai), and LR3 (Taechung, Taichong). Those acupoints are selected because they are well-known meridians for treating gastrointestinal disorders including low abdominal pain and are currently employed in our Korean oriental medical clinic.

Patients, physicians, and nurses are blinded to which intervention patients are allocated, electroacupuncture versus sham acupuncture.

#### Intervention group II: sham electroacupuncture

Patients in the sham acupuncture group receive fake electroacupuncture with a Park Sham Device (PSD). The PSD is a device designed for sham acupuncture which gives little stimulation but a fake sound. The PSD has a PG-306 electric pulse generator, just as in the true acupuncture. However, in the PSD, the internal wire inside PG-306 is cut so as not to deliver the electric pulse to patients, and the patients only hear continuous sound (fake sound) which resembles the electrostimulation.

Schedules for service and acupuncture sites are the same as in the electroacupuncture group.

Patients, physicians, and nurses are blinded to which intervention patients are allocated, electroacupuncture versus sham acupuncture.

#### Control group

Patients in the control group receive routine standard postoperative care without acupuncture.

#### Routine postoperative care for all participants

Routine NSAID (nonsteroidal anti-inflammatory drug) injection for postoperative pain control every 8 hours/additional injection on patient’s requestStart sips of water after bowel sound is checked by auscultation, unless patient complains of nausea or vomitingStart soft diet after sips of water when patient is able to walk independently without nausea or vomitingNo patient controlled anesthesia (PCA)

### Outcomes

#### Primary outcome

The primary outcome is time to first passing flatus after operation.

#### Secondary outcomes

Secondary outcomes include postoperative pain, analgesics, nausea/vomiting, bowel motility, time to tolerable diet, complications, hospital stay, readmission rates, time to recovery, quality of life, medical costs, and protocol failure rate.

Postoperative pain will be checked regularly three times a day and will be recorded using the visual analog scale.

Intravenous analgesic injections will be counted daily.

Nausea and vomiting will be counted daily.

Bowel motility will be checked regularly three times a day, by attending surgeons. Bowel sound will be counted in a minute by auscultation.

Postoperative complications will be checked according to Accordion Severity Classification of Postoperative Complications [13].

Time to recovery is defined as time to ambulate and perform self-care by patient himself or herself.

Discharge is recommended when the patient meets ***discharge criteria*** as follows:Controllable pain with analgesicsNo nausea/vomitingPassing flatus or fecesToleration of soft dietMobilization (independent walking) and self-careControlled complications less than moderate by Accordion system (Table 1)

**Table 1 Tab1:** Accordion severity classification of postoperative complications: expanded classification [13]

1. Mild	Requires only minor invasive procedures that can be done at the bedside such as insertion of intravenous lines, urinary catheters, and nasogastric tubes, and drainage of wound infections. Physiotherapy and the following drugs are allowed: antiemetics, antipyretics, analgesics, diuretics, electrolytes, and physiotherapy.
2. Moderate	Requires pharmacologic treatment with drugs other than those allowed for minor complications, for instance, antibiotics. Blood transfusions and total parenteral nutrition are also included.
3. Severe	Invasive procedure without general anesthesia. Requires management by an endoscopic, interventional procedure or re-operation^a^ without general anesthesia.
4. Severe	Operation under general anesthesia. Requires management by an operation under general anesthesia.
5. Severe	Organ system failure.^b^
6. Death	Postoperative death.

^a^An example would be a wound re-exploration under conscious sedation and/or local anesthetic

^b^Such complications would normally be managed in an increased acuity setting, but in some cases patients with complications of lower severity might also be admitted to an ICU

Quality of life will be assessed by SF-36 Health Survey questionnaire [14], on first outpatient clinic visit.

### Participant timeline

Patient enrollment will be done before operation. After eligibility screen, an informed consent will be obtained at outpatient clinic, emergency department, or ward. After enrollment, random allocation will be performed using blocks. The interventions (electroacupuncture or sham electroacupuncture) will be given twice a day after operation, from operation day to postoperative day 2. All clinical outcome variables will be assessed from operation day until discharge day; except for quality of life, readmission, medical costs, and protocol failure, which will be assessed on the first visit day (postoperative day 7) after discharge (Table 2).

**Table 2 Tab2:** Time schedule of enrollment, interventions, and assessments

	Study period							
	Enrollment	Allocation	Post-allocation					Close-out
TIMEPOINT	-t_1_	0	t_0_	t_1_	t_2_	…	t_x_	t_x+1_
Enrollment:								
Eligibility screen	X							
Informed consent	X							
Allocation		X						
Interventions:								
Electroacupuncture			X	X	X			
Sham electroacupuncture			X	X	X			
Control								
Assessments:								
Passing flatus			X	X	X	X	X	
Postoperative pain			X	X	X	X	X	
Analgesics			X	X	X	X	X	
Nausea/vomiting			X	X	X	X	X	
Bowel motility			X	X	X	X	X	
Tolerability to diet			X	X	X	X	X	
Complications			X	X	X	X	X	
Time to recovery			X	X	X	X	X	
Fulfillment of defined discharge criteria			X	X	X	X	X	
Patient’s agreement to discharge			X	X	X	X	X	
Quality of life								X
Hospital stay								X
Readmission rate								X
Medical costs								X
Protocol failure rate								X

-t_1,_ time before operation; t_0_, operation day; t_1_-t_x_, postoperative day 1 to postoperative day *X* (= actual discharge day); t_x+1,_ the first visit day on outpatient clinic after discharge

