### Methods: assignment of interventions

#### Allocation

Allocation sequence will be generated using block randomization with StatsDirect 3 software by a randomizing person at the study center. After obtaining an informed consent from an eligible patient, the recruiter will be given a treatment code assigned to the patient from the centrally generated allocation sequence to which access is restricted for the recruiter.

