#### Consent/confidentiality

Attending surgeons will obtain written informed consent from all trial participants before inclusion. All collected data will be kept confidential at all times.

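### Allocation appears to come before surgery, but some exclusions arise during it, and this is not reconciled with intention to treat

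*Protocol article*

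**What the plan says.** Timing of allocation, from the Protocol article:

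- Participant timeline: "Patient enrollment will be done before operation", followed by "After enrollment, random allocation will be performed using blocks".
- Allocation: once an eligible patient has consented, "the recruiter will be given a treatment code assigned to the patient".
- Table 2: allocation is at timepoint 0, and the next column, the first under the post-allocation heading, is "t_0_, operation day".

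Eligibility (Exclusion criteria): one criterion reads "Patients who need postoperative fasting according to preoperative evaluation or intraoperative findings". Others exclude patients whose operation is converted to open surgery, patients with another disease diagnosed before or during the operation, and patients who need a combined procedure.

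Analysis (Trial design, and likewise the Abstract): "Data analysis will be performed according to the intention-to-treat principle".

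Who knows what: under Consent/confidentiality, "Attending surgeons will obtain written informed consent from all trial participants before inclusion". The Blinding section conceals electroacupuncture from sham but says that the control group cannot be blinded.

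Timing of treatment (Intervention group I): "At least 2 hours after the operation, electroacupuncture is given for 30 minutes, twice a day". The Sample size/recruitment section starts the primary endpoint clock at the end of the operation.

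**The concern.** If the code is issued before surgery, a patient can be randomised and then meet an exclusion criterion on the operating table. The plan then gives two incompatible instructions: the eligibility section says the patient does not belong in the trial, and the intention-to-treat statement says the patient must be analysed in the allocated arm. The article gives no rule for choosing between them.

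Either choice has a cost. Removing such patients breaks the randomised comparison and uses up patients that the sample size had set aside for ordinary drop-out. Keeping them means analysing patients the protocol calls ineligible, some of whom may be fasting, on an endpoint that measures bowel recovery.

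There is also a possible route to bias. Decisions such as whether a patient needs fasting involve judgement. If the person judging knows that the patient is a control, exclusion may not be independent of the arm.

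**Working it through.** **1. Order of events.** Enrolment is before the operation, allocation follows enrolment, and the code follows consent. Table 2 puts allocation before the operation day. Nothing in the article holds the code back until surgery ends. Allocation before surgery is therefore the natural reading, although no single sentence says so.

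**2. When each exclusion can become known.**

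| Exclusion | When it can be known |
|---|---|
| Conversion to open surgery | only during the operation |
| Another disease | before or during (stated) |
| Need for fasting | before or during (stated) |
| Combined surgery | no timing stated; can be either |

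**3. The plan's own sample size.** Inputs from Sample size/recruitment: means 14.77 and 18.50 h, SDs 4.99 and 4.22 h, 80 % power, 5 % significance, 10 % drop rate. Two-sided testing is assumed.

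- Difference: 18.50 − 14.77 = 3.73 h.
- Pooled SD: √[(4.99² + 4.22²)/2] = √21.35 = 4.62 h.
- Two-sample t-test (noncentral t with 2n − 2 degrees of freedom and noncentrality (3.73/4.62)·√(n/2)): power is 79.9 % at n = 25 and 81.4 % at n = 26, so 26 per arm are needed.
- Drop-out: 26/0.90 = 28.9, rounded up to 29; 29 × 3 = 87. This matches the stated figure.

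The article does not say which difference and SD were used, so this is a reconstruction. On it, the whole allowance is 29 − 26 = 3 patients per arm.

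**4. Effect of removing intraoperative exclusions.** The documents give no rate x, so 3 to 10 % is assumed.

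- Left after these exclusions alone: 29(1 − x).
- Evaluable after the planned drop-out as well: 29(1 − x)(0.90).
- Randomised per arm needed to restore 26 evaluable: 26/[(1 − x)(0.90)], rounded up.

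| x | After exclusions alone | After drop-out too | Power at 3.73 h | Needed per arm (total) |
|---|---|---|---|---|
| 0 % | 29 | 26.1 | 81 % | 29 (87) |
| 3 % | 28.1 | 25.3 | 80 % | 30 (90) |
| 5 % | 27.6 | 24.8 | 78–80 % | 31 (93) |
| 10 % | 26.1 | 23.5 | 76 % | 33 (99) |

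Power is read at whole numbers of patients: 25 at 3 %, 24 to 25 at 5 %, 23 at 10 %. At x = 10 %, 29 × 0.10 = 2.9, so these exclusions alone take the three patients per arm.

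**5. Sensitivity to the effect assumed.** For the second contrast quoted from the cited study (3.40 h, pooled SD 4.84 h), power is 70 % at 26 per arm, 68 % at 25 and 64 % at 23. The loss from the exclusions, 2 to 6 points, is similar in size.

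**The case against.** Several stronger readings are tempting, and the documents do not support them.

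**That all four exclusions can only be found in theatre.** Only conversion is of that kind. Screening includes CT or ultrasonography (Patient screening), so some of the other cases may be caught before allocation; how many is unknown.

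**That the article states randomisation before surgery and removal of these patients afterwards.** It states neither outright. Timepoint 0 is not defined in the Table 2 footnote, and t_0 is a day, not the moment of surgery. No rule for removing randomised patients is given. Handling of randomised but ineligible patients is often left to a full protocol or analysis plan, and the protocol failure rate, listed as an outcome but not defined, might be where they are counted. This reduces the point to an unreconciled conflict, but does not dissolve it. When allocation takes place is trial conduct, and an analysis plan cannot move it.

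**That the operating surgeon knows the arm when deciding on exclusion.** This joins separate statements: attending surgeons take consent, an unidentified recruiter gets the code, and controls are unblinded. The article does not say that the recruiter is the surgeon, or that the consenting surgeon operates. Nothing prevents it either, so the route is possible but not shown.

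**That power collapses if such patients are kept.** With 10 % retained at n = 29, simulated t-test power is about 77 % if their flatus time equals the untreated mean, and about 30 % if their ileus lasts 24 h longer (SD 12 h). The exclusion rate, the 24 h and the 12 h are all absent from the documents. In that extreme case a rank test keeps about 64 %, so much of the fall reflects the t-test's sensitivity to outlying values rather than the timing of allocation.

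It is also fair to say that exclusion alone costs little: at 10 % it leaves 26 per arm, the planned evaluable number, with 81 % power.

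**Conclusion.** The point holds as a conflict between sections. On the natural reading of the timeline, a patient can be allocated and then become ineligible during surgery, and the eligibility section and the intention-to-treat statement then require opposite things. This is certain in kind for conversion and possible for the other three criteria.

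The numerical cost of removal is modest. Power falls from 81 % at the planned 26 evaluable per arm to about 76–80 %. This rests on an assumed exclusion rate of 3 to 10 %, the planned 10 % drop-out on top, a 3.73 h difference, a pooled SD of 4.62 h and a two-sided t-test. The case for change therefore rests mainly on the undefined analysis population and the possible bias in comparisons with control, and on how easily both can be avoided.

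**What to change.** Keep consent and screening before surgery. Release the allocation only after the operation has ended, once the surgeon has recorded that no intraoperative exclusion applies, and before the first possible treatment at 2 hours. Count patients who meet an exclusion during surgery as screening failures before randomisation. State this in the Participant timeline and Allocation sections. Neither the treatment schedule nor the endpoint definition needs to change, and the target stays at 87.

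For patients already randomised, keep all of them in the intention-to-treat set and report intraoperative exclusions by arm.

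Cost: a short amendment, and an allocation service that can be reached after evening operations. Because recruitment opened in June 2015, the change creates two allocation regimes in one trial, and the report must say so and give the date of the switch.

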### Methods: data collection, management, and analysis

#### Data collection methods

All data will be collected using the daily assessment form and will be recorded in case record form, from operation day to discharge day (Table 3). Postoperatively, on the first visit to the outpatient clinic, a quality of life questionnaire (SF-36) will be filled in by the patient.

**Table 3 Tab3:** Daily assessment form: from operation day to discharge day

		Operation	POD1	POD2	POD3	POD4	POD5	…….	Discharge
Pain score (VAS)	1) Morning: ___								
	2) Mid-day: ___								
	3) Evening: ___								
IV analgesics	___/day								
Nausea/vomiting	Nausea: No/Yes(___/day) Vomiting: No/Yes(___/day)								
Bowel motility (bowel sound/minute)	1) Morning: __/min								
	2) Mid-day: __/min								
	3) Evening: __/min								
Intestinal passage	Flatus: Yes(___/day)/No								
	Stool: Yes(___/day)/No								
Tolerability to liquid	Yes/No								
Tolerability to soft diet	Yes/No								
Mobilization and self-care	Yes/No								
Postoperative complications (Accordion classification)	No/ 1/ 2/ 3/ 4/ 5								
Fulfillment of defined discharge criteria	___/total(5)								
Patient’s agreement to discharge	Yes/No								

*VAS* visual analogue scale, *POD* postoperative day

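### Complications are recorded only until discharge despite a scheduled postoperative day 7 visit, so later ones without readmission are lost and follow-up may differ between arms

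*Protocol article*

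**What the plan says.** Complications are a secondary outcome: "Postoperative complications will be checked according to Accordion Severity Classification of Postoperative Complications". Three places in the article fix when they are recorded.

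- **Participant timeline, text:** "All clinical outcome variables will be assessed from operation day until discharge day". The four exceptions (quality of life, readmission, costs and protocol failure) are items "which will be assessed on the first visit day (postoperative day 7) after discharge". Complications are not one of them.
- **Participant timeline, Table 2:** the complications row is marked from the operation day to t_x, which the footnote defines as the "actual discharge day". The close-out column is blank for complications. It is marked for quality of life, hospital stay, readmission, costs and protocol failure.
- **Data collection methods, Table 3:** the Accordion grade is a row of the "Daily assessment form: from operation day to discharge day", and the section says that data "will be recorded in case record form, from operation day to discharge day". The only form that this section adds for the outpatient visit is the SF-36.

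Hospital stay is itself an outcome, listed directly after complications: "time to tolerable diet, complications, hospital stay, readmission rates, time to recovery". The discharge criteria under Secondary outcomes cover pain control, absence of nausea and vomiting, passage of flatus or stool, soft diet, mobilization with self-care, and complications that are controlled and below moderate grade. Statistical methods names the chi-square or Fisher's exact test for categorical data and states no allowance for time at risk.

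**The concern.** There are two separate consequences.

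**Lost events in every arm.** Table 1 grades bedside drainage of a wound infection as mild and antibiotic treatment as moderate. Both can be handled without readmission. If they arise between discharge and the day 7 visit, no scheduled item captures them. If the patient is readmitted, the event appears under readmission, for which no Accordion grade is specified.

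**A window that can depend on treatment.** Flatus, diet, pain and mobilization are what electroacupuncture is meant to improve, and they are also conditions for discharge. If it works as hoped, treated patients may leave earlier and be observed for fewer days. Two arms with the same true risk would then show different recorded proportions, with the lower one in the arm that left sooner. The control group is also unblinded, so discharge timing relative to control could differ for reasons other than recovery.

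At stake is the credibility of the complication comparison in a trial that says it will report both merits and demerits of electroacupuncture. The collection rule is stated explicitly. A statistical analysis plan could adjust for days in hospital, but it could not recover events that were never collected.

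**Working it through.** **The plan's own figures.** The article gives no complication rate, onset pattern or length of stay, so there is no figure on this point to reproduce. Its only computed design figure is 29 patients per arm. That follows from the first quoted contrast in the sample size section: difference 18.50 − 14.77 = 3.73 h; pooled SD √((4.99² + 4.22²)/2) = 4.62 h; a two-sided 5 % t-test with 80 % power needs 26 per arm; 26/0.9 = 28.9, rounded up to 29. It is used below only as the arm size.

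**Simple proportion.** Under a constant daily hazard and a low risk, recorded complications are roughly proportional to days observed. Take a 3-day (72 h) stay in the comparison arm, which is an assumption.

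- If stay falls by the whole flatus difference: 3.73/72 = 0.052, about 5 % fewer recorded. The second quoted contrast, 18.17 − 14.77 = 3.40 h, gives 3.40/72 = 0.047.
- If stay falls by half a day: 1 − 2.5/3.0 = 0.167, about 17 % fewer recorded.
- Days unobserved before day 7 with a 3-day stay: 7 − 3 = 4 of 7.

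**In events.** Let R be the true risk to day 7, identical in both arms, and H = −ln(1 − R). The risk recorded by a discharge at t days is 1 − exp(−H·(t/7)^k), where k = 1 is a constant hazard. A stay shorter by 3.73 h is 3 − 3.73/24 = 2.84 days. With k = 1:

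| True risk to day 7 (assumed) | Recorded, 3.0 days | Recorded, 2.84 days | Recorded, 2.5 days | Gap per 29 patients (2.84 / 2.5 vs 3.0 days) |
|---|---|---|---|---|
| 5 % | 2.17 % | 2.06 % | 1.82 % | 0.03 / 0.10 |
| 10 % | 4.42 % | 4.19 % | 3.69 % | 0.06 / 0.21 |
| 20 % | 9.12 % | 8.67 % | 7.66 % | 0.13 / 0.42 |

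**Wider assumptions.** Let k run from 0.7 (earlier onset) to 1.5 (later onset), R from 5 % to 20 %, and stays be 2 vs 2.5, 2 vs 3 and 3 vs 4 days. With no true difference, the recorded risk ratio (earlier over later discharge) is then 0.55 to 0.86. The gap is about 0.1 to 0.9 events per 29 patients.

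**Lost events.** This part needs no difference in stay. At R = 10 %, constant hazard and a 3-day stay, 1 − 4.42/10 = 56 % of complications to day 7 begin after discharge. Over the same assumptions, with stays of 2 to 4 days, the share is 30 % to 84 %. Those leading to readmission would still surface as readmissions.

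**With a common window to day 7**, both arms record R and the ratio is 1.00 under every scenario.

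**The case against.** The strongest case on the other side has five parts.

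- **Size.** The documents quantify no difference in stay. Their only effect size is 3.73 h (or 3.40 h) on flatus, and half a day is more than three times that. Full carry-through to discharge is doubtful: flatus is one of several discharge criteria, and in the reference study it came at about 15 to 18 h. The Discussion itself expects fast recovery and a possible null result. This stands, and it is why the size is given as a range.
- **Bias as a fact.** A reader might infer that the complication comparison is biased towards electroacupuncture. The documents do not support that. It requires a difference in stay and complications that begin after discharge, and neither is established. The Background credits shorter stay to enhanced recovery programs; for electroacupuncture it says only that recovery might be faster.
- **Harm missed altogether.** A reader might also infer that all early post-discharge harm is missed. It is not: readmission is assessed in every arm at the outpatient visit, so the more serious events surface there.
- **The discharge rule.** Patients with moderate or worse complications do not meet the discharge criteria and so stay under observation. The constant-hazard, fixed-stay model is therefore only an illustration. However, the rule concerns complications already present at discharge, not those that start later.
- **Legitimate choice.** In-hospital complications plus readmission is a coherent definition, and a single visit relies partly on recall. Both are fair. They bear on how to report the outcome, not on whether to collect it when the visit already exists.

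**Conclusion.** The point holds in a limited form. The article explicitly ends complication recording at discharge, so complications that arise later without readmission are lost in all arms, and those with readmission have no Accordion grade specified. That much follows from the text alone.

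The between-arm distortion is conditional. If electroacupuncture shortens stay, equal true risks would show as about 5 % to 17 % fewer recorded complications in the earlier arm. This assumes a constant hazard, a stay of about 3 days and a reduction of 3.73 h to half a day. Larger gaps in stay would give more. In every scenario examined the difference is under one event per 29 patients, so it bears on a descriptive safety statement far more than on any significance test. The primary endpoint and the sample size are unaffected. The change is worth making because it is cheap, not because the trial's main conclusion is at risk.

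**What to change.** - At the existing postoperative day 7 visit, record for every patient any complication since discharge, with Accordion grade and date of onset. Include those that led to readmission.
- Mark complications in the close-out column of Table 2, and add them to the exceptions in the Participant timeline text.
- Compare arms on complications with onset from operation day to day 7. Table 2 defines close-out only as the first outpatient visit after discharge, so use the onset date to cut off at day 7 when the visit falls later, and report how many patients in each arm were not followed to day 7.
- Report in-hospital complications separately, so that the daily ward data remain visible alongside the partly retrospective visit data.

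The cost is one more item at a visit already scheduled for all arms, some reliance on patient recall, and somewhat higher reported complication rates. No treatment or discharge rule changes.
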